## Abstract

**Background:**

Anaemia following hip fracture is common. Approximately 30 to 45% of patients have haemoglobin concentrations below population norms on admission, and around 10% are severely anaemic. Anaemia on admission, and in the postoperative period, is associated with poor outcomes with regard to mobility, postoperative mortality and readmission. There is currently no clear consensus on the optimal method of managing perioperative anaemia in this group of frail patients with frequent comorbidity. Liberal red cell transfusion in the postoperative period does not appear to improve outcome, whereas tranexamic acid appears to reduce transfusion rate at the expense of increased cardiovascular morbidity. There are encouraging results from one centre with the use of agents to stimulate red cell production, including intravenous iron and erythropoietin. UK practice differs significantly from these patients and these studies, and it is not clear whether these promising results will translate to the UK population.

**Methods/Design:**

This is a single-centre randomized controlled parallel group trial, in a British university hospital.Randomization is achieved using a website and computer-generated concealed tables. Participants are 80 patients 70 years or over with acute hip fracture undergoing operative repair. The intervention group receive three daily infusions of 200 mg iron sucrose, starting within 24 hours of admission. The control group receive standard hospital care at the discretion of the clinical team. Red cell transfusions for each group are given in accordance with standard clinical triggers. The primary outcome is an increase in mean reticulocyte count in the intervention group at day 7. Secondary outcome measures include haemoglobin concentrations, early and late transfusion rates, infectious and cardiovascular complications, mobility and 30-day mortality.

**Discussion:**

This is a pilot study to demonstrate haematopoietic efficacy of intravenous iron in this setting. Hence, we have chosen to measure change in reticulocyte count rather than the more clinically relevant differences in haemoglobin concentration or transfusion rate. If our results are positive, the study will provide the necessary information for development of a full-scale trial of intravenous iron.

**Trial registration:**

Current Controlled Trials ISRCTN76424792; UK Medicines and Healthcare products Regulatory Authority (EuDRACT: 2011-003233-34).

## Background

Anaemia following hip fracture is common. Approximately 30 to 45% of patients have haemoglobin concentrations ([Hb]) below population norms on admission and around 10% are severely anaemic. The average fall in [Hb] between admission and postoperative nadir is around 2 g/dl. Various authors [1-4] have found [Hb] on admission to be an independent risk factor for early [1,2] and late [3] postoperative mortality. Foss and colleagues [5] found postoperative [Hb] < 10 g/dl to be an independent risk factor for poor mobility in previously mobile patients, whilst Lawrence and colleagues [6] found that walking distance was strongly correlated with [Hb] > 10 g/dl. In healthy older people, mobility is better in individuals with [Hb] > 12 g/dl [7]. Health outcomes in the general older population are worse in the presence of anaemia [8].

Anaemia in the older hip fracture population is multifactorial. Ageing per se does not appear to cause anaemia [9], but ageing may be associated with reduced haematopoietic reserve, making anaemia more likely in the face of nutrient deficiency or blood loss [10]. In the community, 20% of women aged 80 to 85 are anaemic, with anaemia of chronic disease being the most common cause. These patients represent a major proportion of the hip fracture population. However, 30 to 45% of hip fracture patients are anaemic on admission [11], which may reflect frailer patients having poorer nutrition, being more likely to sustain hip fractures and subsequently having their [Hb] fall further, owing to acute fracture-related blood loss.

Pre-existing anaemia on admission is further exacerbated by the effects of intravenous rehydration, and small but significant intra-operative blood loss results in between one-third and two-thirds of patients receiving blood transfusions within the first few days following operation [5]. The likelihood of transfusion is related to fracture type: subtrochanteric and trochanteric fractures have the highest transfusion rates in both anaemic and nonanaemic subjects. Poor nutrition in the postoperative period is also unlikely to replenish iron stores. Surgery itself may further induce a functional iron deficiency due to humoral suppression of erythropoiesis [12]. Functional iron deficiency does not respond well to oral iron, as iron stores may be normal, and this suppresses intestinal absorption of iron. Indeed, postoperative oral iron has been shown to be of no benefit and also has a high incidence of side effects [13]. Whereas blood transfusion improves [Hb], some authors have found an association between transfusion and improved mobility [5]; others have not found this association, but found that transfusion might reduce readmission rates [14]. Infection rates may also be increased with the use of blood transfusion [15] and there are significant financial constraints with the current cost of a unit of blood in the UK around £200. A recently reported North American trial assessed the effects of liberal versus restrictive postoperative transfusion strategies following hip fracture in patients with cardiovascular risk factors [16-18]. That study found no differences in self-reported mobility or death at 60 days, though there was an increase in cardiovascular complications in the restrictive group. It would seem therefore, at this time that anaemia is a poor prognostic factor but that red cell transfusion does not necessarily alter outcome.

Alternatives to blood transfusion include reduction in blood loss in the perioperative period; stimulation of erythropoiesis with erythropoietin; and oral or intravenous iron.

Pharmacological reduction of blood loss with tranexamic acid has been assessed recently [19]. Although there was a trend to reduced transfusion requirements and reduced postoperative infections, there was also a trend towards increased thrombotic events in the tranexamic acid group and it is therefore not a recommended therapy in this group, despite being advocated for patients with multiple traumas [20].

Erythropoietin has been used in older people to stimulate erythropoiesis. However, the side effects of erythropoietin (hypertension, risks of thrombotic events) make it unattractive in the hip fracture population and the cost of erythropoietin used in these studies is high, over £200 per patient.

Intravenous iron is an attractive therapy in this population. Intravenous iron bypasses the intestinal barrier to absorption [21] that may be seen in functional iron deficiency and stimulates erythropoiesis. The effects of i.v. iron are believed to last for around 7 days, which covers the at-risk period for patients with hip fracture. In post-partum women, who commonly have moderate blood loss during delivery, i.v. iron has been shown to have a faster effect on [Hb] than oral iron [22]. Intravenous iron is believed to be much less likely to cause adverse reactions than in the past, following changes in its pharmaceutical preparation. Iron sucrose is associated with the lowest rate of life-threatening adverse events of all the i.v. iron preparations and these are considerably lower than transfusion-related severe side effects (0.11/million versus 10/million) [23]. Four studies from a Spanish group have reported the effects of i.v. iron on transfusion requirements, mortality and outcome compared with historical controls [21]. Cuenca and colleagues [24] reported a nonsignificant reduction in transfusion rate in patients with trochanteric fractures (55% vs. 44%). A prespecified subgroup of patients with [Hb] >12 demonstrated a significant reduction in transfusion rate (41% vs. 26%). In another retrospective study, transfusion rates were halved (37% vs. 15%) as were the number of units transfused, length of acute hospital stay and 30 day mortality [21]. In a parallel group study [25], transfusion rates were also more than halved (70% vs. 24%) as were the number of units transfused and postoperative infection rates. Recently, the same group have reported on a randomized controlled trial of intravenous iron therapy [26]. No difference was found in transfusion rates for the trial as a whole, but prespecified subgroup analysis demonstrated a reduction in transfusion requirements for patients with subcapital fractures and those admitted with [Hb] > 12 g/dl. Overall there is a reduction in both red cell transfusion and postoperative infection of around 40%; 30-day mortality and length of stay do not appear to be altered. Laboratory data support the positive effects of i.v. iron on erythropoiesis with statistically and clinically significant increases in reticulocyte counts and iron indices. These data used non-randomized comparison groups, except for the final study. Furthermore, clinical management is different from current UK practice and guidelines, with an average time to theatre of over 4 days, compared with a UK median time of around 48 hours [27]. Recent changes to UK tariffs strongly encourage operation within 36 hours [28,29].

Intravenous iron therapy is relatively inexpensive; 200 mg of iron sucrose costs around £15. Administration costs for i.v. iron are likely to be similar to blood transfusion, in terms of consumables and nursing time. Even if the only benefit of intravenous iron is to reduce transfusion rates, the potential cost savings are considerable. Potential benefits, such as a reduction in infectious complications, which are suggested by the current literature, would result in significant cost savings to the healthcare economy, as well as improved quality of care. The direct consumable costs are probably slightly in favour of i.v. iron. With an estimated i.v. iron cost of £43 and blood unit cost of £200, assuming that an average of two units are transfused when given, if i.v. iron reduces transfusion rates from 38% to 25%, the direct cost saving in transfusion-related costs is around £10 per patient. Unlike cost savings from length of stay, these are direct savings to the healthcare system that can be realised, as well as releasing a scarce resource for use elsewhere.

The current literature supports the hypothesis that i.v. iron might be an effective and safe treatment, reducing the need for blood transfusion following hip fracture. Given the differences between UK and Spanish hip fracture management, particularly regarding time to operation, it is unclear whether the promising results from the Spanish experience will be applicable to the UK hip fracture population. It is unknown at present whether i.v. iron would have sufficient erythropoietic effect in hip fracture patients to reduce transfusion rates in the early postoperative period.

A large randomized controlled trial of preoperative i.v. iron for patients with hip fracture may be appropriate. To inform appropriate design of such a trial, a pilot study evaluating the haematological effect of i.v. iron in this population is required.

## Methods/Design

### Study objectives

#### ***Primary aims***

To investigate whether intravenous iron given as three 200 mg doses over three days in patients with hip fracture causes an increase in reticulocyte count in the early postoperative period;

#### ***Secondary aims***

To discover whether intravenous iron has beneficial effects on other measures of haematopoiesis, transfusion requirements and patient outcomes.

#### ***Haematological measures***

As haematopoietic indices, full blood count and serum transferrin receptor concentrations will be measured. These will be collected daily for 7 days following admission. In addition, the number of patients requiring blood transfusion during hospital admission and the transfusion index (units/patient) will be determined.

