### Randomization and blinding

Randomization (on a one-to-one allocation basis) is via a password-protected web-based randomization service provided by the Clinical Trials Support Unit and the sequence is not revealed until datalock. Participants are randomized within 24 hours of admission, either before or after surgery.

The treating team, research nurse collecting data and research team analyzing data will be blinded to treatment allocation. The laboratory will be blinded to treatment allocation. The patient and ward nursing staff will not be blinded, for practical reasons (Venofer is a dark brown, aqueous solution). There is no placebo.

Postoperative data collection is by a research nurse blinded to treatment allocation. The decision that a patient is medically fit for discharge is made by the multiprofessional team, when all are satisfied that the participant has no ongoing needs for acute hospital care. This team is blinded to participant allocation.

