### Inclusion criteria

Patients listed for or having undergone surgical repair of fractured neck of femur, who are aged 70 years or over and are admitted directly to the study centre through the emergency department will be included.

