### Transfusion triggers

Perioperative transfusion will be at the discretion of the attending anaesthetist. Transfusion following return to the ward will be at the discretion of the ward team. Indications for transfusion are, in order of clinical priority:

• Ongoing blood loss with hypovolaemia;

• Symptomatic anaemia: anaemia with haemoglobin concentration < 10 g/dl associated with persistent hypotension, angina, heart failure or cerebral dysfunction;

• Asymptomatic anaemia with haemoglobin concentration < 8 g/dl;

• Relative anaemia ([Hb] significantly less than normal for the patient) and poor functional recovery.

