### Statistics

Data will be analyzed by the research team in conjunction with a medical statistician, using the latest version of SPSS software. There will be no interim analysis.

The primary outcome measure, difference in mean reticulocyte count between groups in the full analysis set will be analyzed using unpaired *t* tests or Mann-Witney tests as appropriate. Differences between groups in maximal change in [Hb], serum transferrin concentration, postoperative mobility, number of units transfused and estimated costs will similarly be analyzed.

Risk ratios will be described for categorical data: the number of patients in each group with cardiovascular or infective complications; and the number of patients requiring transfusion. Descriptive statistics will be used to summarise length of stay and 30-day mortality.

Prespecified subgroup analysis will be undertaken according to admission haemoglobin concentrations ([Hb] <12 or >12 g/dl) and fracture type (sub-trochanteric, extracapsular, intracapsular, pathological).

In addition to the calculated values, confidence intervals and odds- ratios will be presented when appropriate. All clinical information including all adverse events will be presented in full. All secondary analyses will be interpreted with caution as the sample size calculation is based on the primary outcomes only. However, the level of power associated with secondary results will be investigated.

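### Transfusions are counted over the whole admission although patients may be randomised after surgery, so transfusions that iron cannot affect dilute the comparison

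*Protocol article*

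**What the plan says.** **Counting window.** Under Haematological measures, "the number of patients requiring blood transfusion during hospital admission and the transfusion index (units/patient) will be determined". The Statistics section plans a risk ratio for "the number of patients requiring transfusion" and a t test or Mann-Whitney test for units. It gives no start point for either.

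**Entry.** Under Randomization and blinding, "Participants are randomized within 24 hours of admission, either before or after surgery". The Inclusion criteria agree: "Patients listed for or having undergone surgical repair of fractured neck of femur".

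**Transfusion in theatre.** The Transfusion triggers section leaves perioperative transfusion to the anaesthetist. Its listed indications include "Asymptomatic anaemia with haemoglobin concentration < 8 g/dl" and "Symptomatic anaemia: anaemia with haemoglobin concentration < 10 g/dl" when accompanied by certain symptoms.

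**Abstract.** The secondary outcomes named there include "early and late transfusion rates". Neither the Methods nor the Statistics section defines or analyses an early and a late period.

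**Haemoglobin.** The Statistics section compares the groups on maximal change. It gives no direction of change and no rule for values measured after a transfusion.

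**The concern.** A patient operated on soon after admission, transfused in theatre and then randomised has already met the transfusion outcome before allocation. Whatever iron does later, that patient counts as transfused, and the units count in the transfusion index. The whole-admission window is a rule that the article states, so this is not a detail left to a longer document.

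The Discussion names transfusion as the clinical outcome that iron might plausibly improve, and says that a positive pilot will supply the information for a full-scale trial. A risk ratio that mixes in unmodifiable events understates the effect that such a trial would be planned on.

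A lesser concern touches haemoglobin. The Background puts the average fall to the postoperative nadir at about 2 g/dl and places transfusion in the first few days after operation. The Discussion takes day 7 as the time point for the marrow response. The largest change from admission is therefore probably the early surgical fall, and transfusion interrupts that fall in those who drop furthest.

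**Working it through.** **Source of the illustrative rates.** The article gives no power or effect size for transfusion. Its only planning-type rates are the 38% and 25% in the Background's cost example. That example reproduces: 2 units × £200 × (0.38 − 0.25) = £52, less £43 for iron, is £9, against the stated saving of around £10. These are overall rates in a cost argument. Using their ratio, 25/38 = 0.66, as the effect after randomisation is an assumption.

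**Dilution of the risk ratio.** Let f be the share of transfused control patients who were transfused before randomisation. They count in both arms whatever happens later.

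- Iron-arm rate = 0.38·f + 0.38·(1 − f)·(25/38) = 0.25 + 0.13·f
- Observed RR = f + (1 − f)·(25/38)

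The RR depends on f but not on the 38% itself. The documents do not give f. For a range, assume that 20% to 60% are randomised after surgery and that 20% to 40% of the transfused patients among them had blood before randomisation. Assume also that transfusion is equally common in early and late entrants. Then f runs from 0.20 × 0.20 = 0.04 to 0.60 × 0.40 = 0.24.

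| f | Control | Iron | RR |
|---|---|---|---|
| 0 | 38% | 25.0% | 0.66 |
| 0.04 | 38% | 25.5% | 0.67 |
| 0.24 | 38% | 28.1% | 0.74 |

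**What counting from randomisation recovers.** If repeat transfusion is ignored, the control rate becomes 0.38·(1 − f) and the iron rate 0.25·(1 − f). The absolute difference is 0.13·(1 − f) under either count. The ratio returns to 0.66 and the variance falls. The number per arm for 80% power, two-sided 5% (assumed), is

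n = [1.96·√(2p̄(1 − p̄)) + 0.84·√(p₁(1 − p₁) + p₂(1 − p₂))]² / (p₁ − p₂)², where p̄ is the mean of p₁ and p₂.

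- f = 0.04: 38% vs 25.5% needs 218; 36.5% vs 24.0% needs 212.
- f = 0.24: 38% vs 28.1% needs 355; 28.9% vs 19.0% needs 292.

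**Units.** Units given before randomisation add the same expected amount to both arms. The expected difference in mean units is unchanged, but it becomes smaller relative to the total and to its spread. A comparison of units is therefore blunted too.

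**Haemoglobin.** Daily values on days 0 to 7 were simulated with 200,000 patients per arm and a true iron effect of 1 g/dl. The mean fall of 2 g/dl and the 8 and 10 g/dl thresholds come from the article. Admission mean 12.2 and SD 1.6 g/dl, SD of the fall 1.0, a 2 g/dl rise per transfusion episode and a 15% daily chance of symptoms below 10 g/dl are assumptions. About 35% of controls were then transfused.

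| Iron effect | Measure | Without transfusion | With transfusion | Loss |
|---|---|---|---|---|
| Early | Maximal fall | 0.94 | 0.84 | 11% |
| Early | Day 7 | 1.01 | 0.61 | 39% |
| Building from day 2 to 7 | Maximal fall | 0.33 | 0.25 | 24% |
| Building from day 2 to 7 | Day 7 | 1.02 | 0.85 | 17% |

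If the effect is late, the maximal fall shows only a third of it even without transfusion. Timing then matters more than transfusion. Day 7 does better in that case, but it carries donor haemoglobin and does worse if the effect is early.

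**The case against.** The affected group may be small. Entry after surgery needs both operation and randomisation within 24 hours of admission. The article's care standard is operation within 36 hours, and it puts the UK median at around 48 hours. The Background places transfusions in the first few days after operation, so many will follow randomisation. This stands: at the lower end of the illustration the RR moves only from 0.66 to 0.67. The 38% and 25% may also already contain unmodifiable transfusions, which is a further reason to read the range as an illustration.

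The prior transfusions are balanced by randomisation, and blood used per admission suits the cost outcome. Both are true. The whole-admission total can stay for costs, but it is the wrong count for a treatment effect.

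These are secondary outcomes of a pilot, and the Statistics section promises caution. Power to separate 38% from 25% with 40 per arm is only about 24% even without dilution. That limits what the pilot can conclude. It does not justify a start point that counts events from before allocation.

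The abstract's early and late rates could partly answer the point, but only if the split were timed from randomisation. The article does not define it.

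On haemoglobin, the reading below 8 g/dl that prompts transfusion is itself recorded, so much of the nadir survives. This also stands, and it keeps that half of the point minor.

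**Conclusion.** The point holds for transfusion. The stated window, together with entry after surgery and transfusion in theatre, lets events from before randomisation count as outcomes. The direction, towards no effect, follows from the text. The size does not: the RR range of 0.67 to 0.74 rests on assumed shares and on a borrowed effect of 0.66, and the true dilution may be negligible.

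A reader might infer that the transfusion result is biased between arms or could show a false benefit. The documents do not support that, because the prior transfusions are balanced in expectation.

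A reader might also infer that transfusion hides or reverses the haemoglobin difference, or that maximal change is taken over unequal numbers of samples. Neither is supported. The simulation shows a reduction of 11% to 24% and no reversal. The article schedules the same daily samples for everyone, and its full analysis set requires a day-7 reticulocyte count. The haemoglobin remark also assumes that maximal change means the fall to nadir, which the article does not state.

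**What to change.** 1. In Haematological measures and Statistics, count patients transfused and units from randomisation in both arms.
2. Report transfusion before randomisation as a baseline characteristic, by arm. Keep the whole-admission total for the cost analysis if wanted.
3. Carry the abstract's early and late transfusion rates into the Methods and Statistics, with the split timed from randomisation.
4. As a supplement, state the direction of the maximal haemoglobin change and add day-7 haemoglobin adjusted for the admission value by ANCOVA. Add a sensitivity analysis for units transfused since randomisation, for example subtracting an assumed amount per unit over a stated range. This need not replace the planned measure, since day-7 values are themselves exposed to donor haemoglobin.

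The cost is a change of wording and one additional analysis. It needs the timing of each transfusion, which should be in the clinical record, and daily blood counts that are already scheduled. The downside is slightly fewer counted events. No change to transfusion practice is involved.
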